### Educational campaign

An educational campaign targeting all personnel who work in Lund’s RR precedes the implementation of the EM in clinical practice. Evidence for the potential benefits of an EM—including results from a locally performed crisis checklist study^22^—is presented, as well as the protocol for EM use. Documenting nurses during priority 1 patient management are taught to log in to the EM, display and navigate between checklists, open popover windows, record whether interventions were not indicated, done before or thanks to checklist access, record the team’s opinion of the EM’s value, request contact with the investigators, and log out. Documenting nurses carry out these functions in addition to their usual documentation tasks.

### Data acquisition

The following data pertaining to each priority 1 patient managed during the 6-month period prior to, and the 6-month pilot study period following implementation of the EM in clinical practice, are extracted from Region Skåne’s clinical databases and the national data registry SVAR (Svenska Akutvårdsregistret):

Patient age and sex, presenting complaint and vital signsPresumptive diagnosis in the RRTime spent in the RR, in the ED, and admitted to the hospitalWhether the patient was admitted to the intensive care unit, and if so duration of admission7-day and 30-day mortality

The following data regarding EM use are recorded on a dedicated computer located within the hospital’s firewall each time the EM is activated during the 6-month pilot study period:

Log-in and log-out timesIdentification number of the nurse who logged in, level of the most senior physician who was physically present at the bedside during patient management, and patient identification number (which is immediately encrypted)Checklists and fact sheets that were displayedWhether interventions were performed before or thanks to checklist access when the EM was used in Do-Confirm mode, or whether the EM was used in Read-Do or Sampling mode insteadThe team’s subjective evaluation of the value of the EM according to a 1–6 Likert scaleReasons for EM non-use despite logging inWhether prompt contact with the research team is requested

The following data are extracted from the medical records of 150 selected cases (see below):

Baseline information regarding the patient’s age, sex, known medical background at the time of presentation and current medicationsClinical information regarding the patient’s presentation to the RR: ambulance report, history that can be obtained in the RR, vital signs, physical findings, ECG, bedside blood test results and point-of-care ultrasound findingsAll interventions (investigations and treatments) performed during the patient’s management in the RRWhether the physician was a specialist or resident, and years of experienceFinal hospital diagnosis pertaining to the presentation in the RR

Figure 1 summarises data acquisition during the study period. The primary investigator alone has access to the encryption key. All investigators have access to the anonymised dataset for analysis purposes.

**Figure 1 F1:**
[figure not shown]
This figure illustrates the two phases of the study, before and after emergency manual implementation, and how data acquisition corresponds to each phase.

### Impact of EM use on resuscitation team performance

The final 50 cases where the EM was used in Do-Confirm mode and interventions were performed thanks to checklist access are identified for external review. The final cases during the 6-month study period are selected to allow personnel the opportunity to integrate the new tool within their clinical practice. The degree to which each intervention is indicated is independently assessed by three specialists in emergency medicine. All three assessors are blinded to whether the intervention was performed before or after EM use. Two assessors are blinded to the content of the EM, while one is involved in the development and use of the EM. Interventions are categorised, based on the available extracted clinical information, as indicated (eg, administering antibiotics to the septic patient), of neutral relevance (eg, measuring liver function tests for the patient with suspected benzodiazepine overdose), or not indicated (ie, overinvestigation or overtreatment, for example, ordering CT to rule out pulmonary embolism for a patient with pulmonary oedema). When the three assessors are not in agreement regarding the degree of indication of the intervention, resolution is reached through discussion, and based on majority opinion if no consensus can be reached. Management is deemed improved when interventions categorised as indicated are carried out thanks to EM use. EM use is deemed to not add value if additional interventions are categorised as of neutral relevance. EM use is deemed detrimental if additional interventions are categorised as not indicated.

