### Objectives

The primary objective of the study is to determine whether Do-Confirm EM use leads to the performance, by resuscitation teams managing priority 1 patients in the ED, of additional interventions that are deemed indicated, of neutral relevance or not indicated given the clinical context. Secondary study objectives are

Determining the frequency and modality (Do-Confirm, Read-Do, Sampling) with which the EM is used and whether these changed significantly over the study period.Determining whether Do-Confirm EM use in selected cases where other modes were used might have led to the performance of additional indicated interventions.Determining the degree to which resuscitation teams find the EM helpful, and under which circumstances.

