### EM: protocol for use

EM use during priority 1 management is strongly advocated but not mandatory. The documenting nurse is assigned the specific task of activating the digital EM. Regarding problem and diagnosis checklists, Do-Confirm is the default mode of EM use—the team first manages priority 1 patients without support from the EM. Once the management plan is finalised (a juncture which may be verbally confirmed with the team leader), the documenting nurse then asks the team: “Which checklist should I display?” When a checklist is displayed, the documenting nurse reads aloud each potential intervention or diagnosis for team consideration. The documenting nurse registers on the digital checklist whether each intervention is

Deemed indicated and has already been carried out.Deemed irrelevant or contraindicated.Deemed indicated and will be carried out thanks to EM use.

The physician responsible for patient management has the mandate to request that the EM not be used, to pause or terminate EM use at any time, and to depart from the recommendations featuring on the checklist. Physicians may also request that the EM be displayed directly and used in Read-Do mode or for retrieval of specific information (Sampling mode). Regarding procedure checklists and fact sheets, the default modes of use are Read-Do and Sampling, respectively. After EM use, teams grade the usefulness of the EM on a 1–6 Likert scale prior to logging out. If the documenting nurse logs in to the EM but the EM is not used, the nurse selects among potential reasons for non-use prior to logging out. Teams can also electronically request contact with the investigators to report specific events related to EM use.

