## Strengths, limitations and significance

The literature on medical crisis checklists argues that specific checklists, used according to clear protocols within specific contexts, improve performance. Yet there are no published data on how the introduction of an EM affects the performance of resuscitation teams during the management of actual priority 1 patients in the ED. The main strength of this study is that it evaluates EM use during the management of consecutive, unselected priority 1 patients by resuscitation teams in the ED.

In this study, some of the data on patient characteristics (such as age, chief complaint) and EM use (duration of use, checklists and fact sheets displayed) are automatically registered. Other EM use data (for instance, subjective team evaluation of the EM value, modality of EM use) are actively registered by the documenting nurse. The study is not a randomised controlled trial of EM use, and whether the EM is used or not is at the discretion of each resuscitation team. While these study aspects limit the evaluation of how routine EM use would impact on performance, the study will provide information about the circumstances under which resuscitation teams voluntarily use the EM and deem that it adds value to clinical practice. The study stretches over a 6-month period, allowing for an analysis of how resuscitation teams integrate a new tool within their clinical practice over time.

The study is not powered nor designed to detect causal relationship between EM use and patient outcome. The study will determine whether interventions carried out thanks to checklist use are indicated, of neutral relevance or not indicated based on the clinical context, as assessed by external reviewers. A limitation of this assessment stems from the fact that the external review is based on information available from patient records, which may not convey all the relevant factors affecting clinical decisions.

This study will be conducted in a single academic Swedish ED, limiting the external validity of the results. Yet this study will provide valuable information to guide the development of a tool that has the potential to improve the management of critical patients, and pave the way to multicentre studies of EM use in the ED.

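### The protocol does not say whether assessors see the final hospital diagnosis; if they do, the primary proportions are open to hindsight bias

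*Protocol article*

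**What the plan says.** Under Objectives, the primary question is whether Do-Confirm EM use leads to "additional interventions that are deemed indicated, of neutral relevance or not indicated given the clinical context".

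Under Data acquisition, a list sets out what is taken from the medical records of the 150 selected cases. These are the 50 EM cases behind the primary outcome and 100 matched cases. The list covers baseline data, clinical information on the presentation to the RR, all interventions performed there, physician grade and experience, and, as a separate last item, the final hospital diagnosis.

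Under Impact of EM use on resuscitation team performance, the basis for grading is: "Interventions are categorised, based on the available extracted clinical information, as indicated", of neutral relevance or not indicated. The blinding rules follow: "All three assessors are blinded to whether the intervention was performed before or after EM use" and "Two assessors are blinded to the content of the EM, while one is involved in the development and use of the EM". For the 100 matched cases, the section on unperformed interventions adds blinding to which interventions were actually carried out. None of these rules mentions the final diagnosis.

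The stated limitation of the review is that it relies on patient records, "which may not convey all the relevant factors affecting clinical decisions". That concerns too little information, not information that came later.

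**The concern.** An intervention is indicated or not in the light of what the team could know at the bedside. An assessor who knows the final diagnosis may grade a reasonable test as indicated because the disease was later confirmed, or as overinvestigation because it was later excluded. The grade would then partly record how the case turned out.

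Three features of the design make this matter here.
- The plan moves directly from the grade to a conclusion: EM use is deemed to have improved management, added no value or been detrimental according to the category assigned.
- The primary outcome is an absolute proportion, set against a fixed 10% in the sample size section. Blinding to before or after EM use protects a comparison between those two groups of interventions. It does not protect the level of the proportion.
- Discussion and majority opinion do not remove an error that all three assessors share because they read the same file.

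A related gap exists for the 100 matched cases. The EM is opened afterwards to see what it would have prompted, but the article does not say what information guides the choice of checklist. In real use the nurse asks "Which checklist should I display" while the final diagnosis is still unknown.

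**Working it through.** **Step 1. What the text settles about the grading file.**

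- *Pointing to the diagnosis being available to assessors.* It is an item in the 150-case extraction. The only stated use of that extraction is the external review: Data analysis plans nothing else for these 150 cases than the proportions in each grade. No blinding rule excludes it.
- *Pointing the other way.* In the extraction list, the words clinical information label the RR-presentation item, and the final diagnosis is a different item. Background and history are limited to what was known or obtainable in the RR. The list also holds physician grade and experience, which is not obviously grading material, so the list cannot simply be equated with the assessors' file.

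The text therefore permits both readings.

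**Step 2. The plan's own figure.** Inputs from Sample size calculation: n = 75 interventions (25 + 2×25), null rate p0 = 0.10, alternative p1 = 0.21, α ≤ 0.05, power at least 80%. Exact one-sided binomial test, with interventions treated as independent:

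- P(X ≥ 12 | 75, 0.10) = 0.069, which is above 0.05.
- P(X ≥ 13 | 75, 0.10) = 0.034, so the cut-off is 13 of 75.
- Power = P(X ≥ 13 | 75, 0.21) = 0.821. At 20% it is 0.760.

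The stated power is reproduced. Nothing in this point disputes it.

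**Step 3. Sensitivity to misgrading.** The documents give no misgrading rate, so every rate below is an assumption. Let p be the rate that would be graded indicated on RR information alone.

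*Net upgrades:* a fraction u of the remaining interventions is moved to indicated. Observed rate = p + u(1 − p). With p = 0.10:

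| u | observed rate | P(X ≥ 13) |
|---|---|---|
| 0 | 0.100 | 0.034 |
| 0.02 | 0.10 + 0.02×0.90 = 0.118 | 0.100 |
| 0.05 | 0.10 + 0.05×0.90 = 0.145 | 0.288 |
| 0.10 | 0.10 + 0.10×0.90 = 0.190 | 0.689 |

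*Net downgrades:* a fraction d of the indicated interventions is moved out of that grade. Observed rate = p(1 − d). With p = 0.21:

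| d | observed rate | P(X ≥ 13) |
|---|---|---|
| 0 | 0.210 | 0.821 |
| 0.10 | 0.21×0.90 = 0.189 | 0.681 |
| 0.30 | 0.21×0.70 = 0.147 | 0.305 |

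In counts, u = 0.05 is 0.05×0.90×75 = 3.4 interventions, and d = 0.10 is 0.10×0.21×75 = 1.6 interventions. A few changed grades among 75 are enough to move these probabilities materially.

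**The case against.** The strongest objection is that no sentence says assessors see the final diagnosis. The phrase used for the grading basis echoes the label of the RR-presentation item, and most of the extraction looks designed to rebuild the team's view at the bedside. The target, "deemed indicated, of neutral relevance or not indicated given the clinical context", fits that intent. The diagnosis could have been extracted only to describe the cases. What goes into an assessor's file is also a detail that a journal article may leave to a review manual.

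Much of this stands. A reader might infer that assessors do grade with the final diagnosis in hand and that the primary outcome therefore carries hindsight bias. The article does not support that as fact. Nor do its examples: CT for pulmonary embolism in a patient with pulmonary oedema could be judged from the presentation, and the neighbouring example is framed on a suspected overdose. A reader might also infer that checklists for the matched cases are chosen by final diagnosis. The article does not say so, and its problem checklists are organised by presenting symptoms.

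The numerical illustration has limits too. Its rates are assumed, upgrades and downgrades may partly cancel, and Data analysis describes only descriptive reporting of the proportions. The 10% benchmark belongs to the sample size rationale.

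The plea of condensation does not stand in full. The article itself gives both the extraction list and the blinding rules. Read together, they leave the diagnosis open to the assessors, and the limitations do not address hindsight.

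**Conclusion.** The point holds as an exposure, not as a demonstrated bias. The article extracts the final diagnosis for the reviewed cases, grades on extracted information, and states blinding rules that do not cover the diagnosis. If it is in the grading file, the three primary proportions would partly reflect how the diagnosis turned out, with direction and size unknown.

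The figures show sensitivity only. They rest on 75 independent interventions, an exact one-sided test against 10%, and assumed misgrading rates. They do not estimate what will happen. Confidence is medium because the text allows a reading under which the problem does not arise. The change is still worth making, since grades given with knowledge of the diagnosis cannot afterwards be made blind.

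**What to change.** - In Impact of EM use on resuscitation team performance, state that the assessors' case file contains only information available in the RR. Withhold the final hospital diagnosis until all grades are locked, and use it afterwards only to describe the cases.
- As a parallel precaution in Unperformed interventions recommended by the EM, state that the checklist is chosen from the presenting complaint and the presumptive RR diagnosis by someone who has not seen the final diagnosis. Both items are already collected for every priority 1 patient.

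The cost is about two sentences and one field held back from the file. No new data are needed and no planned number changes. The downside is that assessors grade with less certainty, as the team did.

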### Sample size calculation

There are no published data on EM use during patient management in the ED. We derived a sample of size of 50 patients where at least one intervention was performed thanks to Do-Confirm EM use based on the following assumptions:

Among patients with at least one intervention performed thanks to the checklist, half of these patients will have one such intervention performed while the other half will have two. Hence, 50 such patients should generate 25+2×25 = 75 interventions thanks to the checklist.When multiple checklist-indicated interventions occur in the same patient, the probability of occurrence of these interventions are independent of each other.

In our opinion, a clinically meaningful rate for indicated interventions performed thanks to checklist access is ≥10%. Figure 2 shows that if the true rate of clinically indicated interventions due to the checklist is ≥21% then 50 patients generating 75 interventions will be sufficient to reject the null hypothesis that the indicated rate is ≤10% with at least 80% power and a type I error probability of α≤0.05.

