**Figure 2 F2:**
[figure not shown]
‘Intervention’ refers here to interventions performed by the resuscitation teams thanks to use of the emergency manual. Interventions are graded by external assessors as indicated, neutral or not indicated based on the clinical context. The power curves in the figure plot the power to determine, with p≤0.05, that the proportion of interventions deemed indicated exceeds 10% as a function of the true probability that the intervention is indicated. Assuming that the true proportion of interventions deemed indicated is 21%, 75 interventions are required to meet these requirements. Assuming that half of the patients feature one such intervention and the other half two, then 50 patients can be expected to generate 75 interventions.

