### Data analysis

Descriptive statistics are used to analyse EM use data and determine the following (average over and trends throughout the pilot study period):

Frequency of EM use and mode of use (Do-Confirm, Read-Do or Sampling)Which checklists or fact sheets are most frequently accessedTime between login to and logout from the digital EMSubjective degree of EM value and correlation with specific checklists or fact sheets

Descriptive statistics are also used to determine whether EM use is associated with length of stay in the RR, length of hospital admission and mortality. These analyses are hypothesis-generating and not intended to infer causality. For the 150 patients that are externally reviewed, descriptive statistics are used to report the proportions of interventions deemed indicated, of neutral value or not indicated.

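### The 50 cases are sized for a one-sided test against 10% on 75 interventions treated as independent, but the Data analysis section plans only descriptive statistics for these proportions

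*Protocol article*

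**What the plan says.** The Sample size calculation section sets up a hypothesis test. It aims to "reject the null hypothesis that the indicated rate is ≤10" per cent, "with at least 80% power and a type I error probability of α≤0.05", "if the true rate of clinically indicated interventions due to the checklist is ≥21" per cent. The caption of Figure 2 gives the direction, "that the proportion of interventions deemed indicated exceeds 10" per cent, and the count: "Assuming that the true proportion of interventions deemed indicated is 21%, 75 interventions are required to meet these requirements".

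Two assumptions are listed openly. Half of the 50 patients contribute one intervention and half two, giving 25 + 2×25 = 75. Within a patient, "the probability of occurrence of these interventions are independent of each other".

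The Data analysis section covers the 150 externally reviewed patients, who include these 50. For them, "descriptive statistics are used to report the proportions of interventions deemed indicated, of neutral value or not indicated". It names no test, no interval and no 10% benchmark.

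Among the secondary objectives, the first asks how often and in which mode the manual is used and "whether these changed significantly over the study period". The Data analysis section places averages and trends over the pilot period under descriptive statistics.

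**The concern.** There are two linked problems.

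First, the article gives the primary proportions an analysis that differs from the one used to size the study. A reader cannot tell whether the study will test a hypothesis or describe a proportion, or whether the 10% benchmark will be applied at all.

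Second, the independence assumption is worded for the occurrence of interventions, while a binomial test needs the grades to be independent. Two interventions in one patient share the chart and the clinical context. They are graded by the same three assessors, who settle disagreements by discussion. Some positive correlation between their grades is plausible. If the 75 grades are then analysed as independent, intervals are too narrow and the type I error is larger than its nominal calculation suggests.

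**Working it through.** **Inputs.** From Sample size calculation and Figure 2: null rate 0.10, alternative 0.21, alpha ≤0.05, power ≥0.80, 75 interventions from 25 single and 25 paired patients. The test is taken as one-sided, which the null (≤10%) and the caption (exceeds 10%) imply. The documents give no within-patient correlation of grades (rho), so rho is an assumption shown over a range.

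**1. The plan's own figure.** Exact binomial, n = 75. The smallest cut-off with P(X ≥ r | 0.10) ≤ 0.05 is r = 13.
- Size: P(X ≥ 13 | 0.10) = 0.034.
- Power: P(X ≥ 13 | 0.21) = 0.821.

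The claim of at least 80% is reproduced.

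**2. Allowing for pairs.** For a pair with marginal rate p, P(both indicated) = p² + rho·p(1−p). The exact distribution of the total is the convolution of 25 single patients and 25 such pairs. The variance of the total is p(1−p)(75 + 50·rho), so the design effect is 1 + (50/75)·rho = 1 + 0.667·rho. At rho = 0.3 this is 1.2 (effective n = 75/1.2 = 62.5). At rho = 0.5 it is 1.333 (effective n = 56.2).

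| rho | size at cut-off 13 | cut-off holding size ≤0.05 | power at 0.21, size held |
|---|---|---|---|
| 0 | 0.034 | 13 | 0.821 |
| 0.1 | 0.039 | 13 | 0.812 |
| 0.2 | 0.044 | 13 | 0.804 |
| 0.3 | 0.049 | 13 | 0.797 |
| 0.34 | 0.050 (just over) | 14 | 0.709 |
| 0.5 | 0.057 | 14 | 0.700 |

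Power drops below 0.80 at rho of about 0.26. Size at cut-off 13 passes 0.05 at about 0.34, and there the cut-off must rise by one.

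**3. Allowing for a different yield.** Same exact rule, cut-off reset each time.
- 60 interventions (40 single, 10 paired), independent: reject at ≥11, power 0.741.
- 65 interventions (35 single, 15 paired), independent: reject at ≥12, power 0.738.
- 100 interventions (50 paired), independent: power 0.915. At rho 0.5, with size held: 0.814.

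Because counts are discrete, power moves in a saw-tooth. Totals of 69 to 71 and of 74 and above also reach 0.80 under independence; 72 and 73 do not.

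**4. Sidedness.** An exact test at one-sided 2.5% (two-sided 5%) rejects at ≥14 of 75 and has power 0.733. A two-sided normal approximation without continuity correction gives 0.815.

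**5. Precision.** At an observed 21% of 75, the approximate 95% half-width is 1.96·√(0.21·0.79·(75 + 50·rho))/75. This is 9.2 percentage points at rho = 0 and 10.6 at rho = 0.5.

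**The case against.** The strongest reply has four parts.

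- **The power is right and its assumptions are declared.** This stands. A reader might infer that the 80% claim is false, or that it holds only at exactly 1.5 interventions per patient. Neither follows: the figure is reproduced, and several other totals also reach 80%.
- **The clustering loss is small unless correlation is strong, and no correlation is documented.** This stands in part. Up to about 0.25 the design keeps 80% power, and at 0.3 the shortfall is 0.3 percentage points with size still under 0.05. The loss becomes material only from about 0.34. But the margin is thin, the true correlation is unknown, and grading the pair from one chart by one panel favours a positive value.
- **A shortfall in yield is only one possibility.** This stands. More interventions per patient would raise power even with correlation, as the 100-intervention case shows.
- **An article leaves test details to an analysis plan.** A reader might infer from the Data analysis section that the test will never be done. The article does not support that: it does not exclude the test, and an analysis plan that is not shown may contain it. The point does not rest on missing detail, however. The article does name an analysis for these proportions, and it is not the one that justified 50 patients.

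**Conclusion.** The point holds as an inconsistency within the article, together with a power statement that has little margin. Sample size calculation and Figure 2 rest on a one-sided test against 10%; Data analysis assigns the same proportions descriptive statistics only. Objective 1 asks about significant change and receives descriptive trends.

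On its own assumptions the stated power is correct, at 82%. With 75 interventions it stays near 80% up to a within-patient correlation of about 0.3 and falls to about 70% at 0.5 with size held. It is about 74% at 60 or 65 independent interventions and about 92% at 100. These figures assume a one-sided 5% count rule, at most two interventions per patient and a common correlation across pairs. A cluster-robust or bootstrap test would give somewhat different values.

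**What to change.** **Data analysis.** Name the primary analysis: a one-sided 5% test of the indicated proportion against 10%, with patient as the cluster (for example a patient-level bootstrap or a cluster-robust method). Report patient-clustered 95% confidence intervals for the indicated, neutral and not-indicated proportions.

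**Sample size calculation.** State that the independence assumption concerns the grades, and that the test is one-sided. Restate power at 21% as about 82% under independence, falling to about 70% at a within-patient correlation of 0.5, with 75 interventions. Alternatively, drop the power claim and justify 50 patients by precision: a half-width of roughly 9 to 11 percentage points at an observed 21%.

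**Objective 1.** Either model manual use (yes or no for each priority 1 patient) on calendar week, or remove the word about significance. Nurse identity should not be the cluster in such a model: by the Data acquisition section it is recorded only when the manual is activated, so patients without a log-in have none.

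**Cost.** A slightly less favourable stated power and slightly wider intervals. No extra patients and no new data.
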